### Data analysis

The primary outcome is the PRWE score at 6 weeks. This outcome is represented as the change in outcome scores from T0 to T2 (delta, T2–T0). An intention-to-treat analysis is performed, and any missing data are imputed. Data will be analysed using a two-sided t-test or the Mann-Whitney U test, depending on normality of the distribution.

For the secondary continuous outcomes (PRWE score at 2 and 12 weeks, ROM, grip strength, pain scores), a repeated measures analysis of variance will be performed, where group assignment (game group vs control group) is the between-subjects factor, and time of visit (baseline, 2, 6 or 12 weeks follow-up) is the within-subjects factor. In case of a non-normal distribution, generalised estimating equations will be used. An intention-to-treat analysis will be performed, and any missing data will be imputed using multiple imputation. Other (secondary) functional outcomes are analysed as a percentage of the unaffected wrist. Bonferroni correction is applied to all secondary outcomes to correct for multiple tests. Therefore, p values of <0.0045 will be considered statistically significant.

Baseline data and secondary outcomes include categorical data such as fracture type and treatment type. These data will be analysed using the Χ^2^ test, and outcomes will be presented as the differences in frequencies. P values of <0.05 are considered statistically significant. Treatment adherence is measured using a self-reported diary. The number of exercise sessions and the total duration of exercising are continuous variables that will undergo quantitative and qualitative synthesis using a two-sided t-test or a Mann-Whitney U test as appropriate.

The diaries that are handed in after the trial period are analysed for the percentage of days the diary is completed and the total estimated time of exercising. In the intervention group, these data are also compared with the total time of exercising as registered within the game. In addition, should not all diaries be completed, the number of diaries handed in after the study period is registered. These data are then analysed using the Χ^2^ test, and outcomes will be presented as the difference in frequencies.

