### Randomisation

When patients have been found eligible, and after they signed the informed consent form, baseline measurements are obtained. After baseline measurements, the local researcher contacts the central research coordinator for randomisation to take place and to receive information on group allocation. Randomisation sequence is determined by an independent researcher using an online automatically generated randomisation list (via www.sealedenvelope.com). Allocation concealment is obtained using sealed opaque envelopes. Patients are randomised using block randomisation in blocks of four, stratified for age (18–64, and 65 years or above) and for treatment type (conservative treatment using immobilisation or operative treatment by means of internal fixation) to ensure a balanced randomisation into the two groups.

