### Outcome measurements

Standard demographic information including age, sex, fracture type according to the Arbeitsgemeinschaft für Osteosynthesefragen/Orthopaedic Trauma Association fracture classification,^39^ and the type of treatment is obtained directly after inclusion. Follow-up visits take place at 2, 6, and 12 weeks postoperatively or after cast removal, for operatively or conservatively treated patients, respectively. A timeline of the trial is shown in figure 3. The primary outcome measure, which is the validated Patient-Rated Wrist Evaluation (PRWE) questionnaire is completed by patients at all follow-up visits.^40 41^ The active ROM is measured in degrees using an analogue universal goniometer. ROM and grip strength are measured in both hands, where grip strength is measured in kilograms, using an analogue hand dynamometer (Baseline, Fabrication Enterprises, White Plains, New York, USA). The maximum value of two measurements with 5 min rest in between is used for analysis. All measurements are performed by a clinician blinded to group allocation that has been specifically trained for this trial, and is experienced in taking ROM and strength measurements in daily practice.

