### Sample size calculation

The primary outcome is the PRWE questionnaire outcome score after 6 weeks of treatment. This questionnaire has been validated previously,^40^ and has a minimal clinically important difference of 11.5, with 1.5 for the pain subscale and 10 for the function subscale.^41^

An elaborate and important Cochrane review on the effect of physiotherapy after distal radius fractures reports only three studies comparing a regular physiotherapy regimen with an unsupervised home-exercise programme.^15^ These comparisons are relevant here, since the use of this serious game can be compared with an unsupervised home-exercise programme. Only one of these three trials reports patient-rated functional outcomes in addition to ROM or grip strength values.^18^ This study looks into the effects of a progressive home-exercise programme, compared with the effect of 12 physiotherapy sessions over a 6-week period in patients with an operatively treated distal radius fracture. They found a positive effect in favour of the home-exercise programme, with PRWE scores of 18.5 (SD 15.9) for the home-exercise group, compared with 36.1 (SD 13.9) in the physiotherapy group after 6 weeks.^18^

As a result, using the SD of 15.9, for a two-sided t-test in two groups with an alpha of 0.05, a power of 90% (1–beta=0.9), an allocation ratio of 1:1, this leads to necessary group sizes of 42 patients per group to detect a clinically relevant difference of 11.5 points at 6 weeks. With a 10% dropout rate, a total of 92 patients are needed for this trial.

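### The primary test leaves out the two randomisation strata, so it is conservative and loses some power if PRWE change differs between strata

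*Protocol article*

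**What the plan says.** The Randomisation section of the protocol article describes "block randomisation in blocks of four, stratified for age (18–64, and 65 years or above". The second stratification factor is whether the fracture was managed in a cast or by surgery. The stated aim is balance between the two groups.

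The Data analysis section defines the primary outcome at 6 weeks: "This outcome is represented as the change in outcome scores from T0 to T2 (delta, T2–T0". The test follows: "Data will be analysed using a two-sided t-test or the Mann-Whitney U test, depending on normality of the distribution". No stratum term is named. The repeated-measures analysis of the secondary continuous outcomes also names only group and visit as factors.

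The Sample size calculation section sizes the trial for the same unadjusted test, "using the SD of 15.9, for a two-sided t-test in two groups with an alpha of 0.05". That SD comes from a trial "in patients with an operatively treated distal radius fracture".

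The Outcome measurements section sets the clock for the visits: "Follow-up visits take place at 2, 6, and 12 weeks postoperatively or after cast removal", according to how the fracture was treated.

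**The concern.** Stratified blocks hold the two arms nearly equal in age group and treatment type. Differences between strata therefore contribute almost nothing to the true sampling variability of the treatment difference. A two-sample test does not know this. It estimates its error from the total spread within each arm, which includes any difference between strata, so its standard error exceeds the true one.

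Because the tested quantity is a change score, what counts is a difference between strata in change. The protocol makes such a difference plausible for treatment type. For operated patients, T0 to T2 covers roughly the first six weeks after surgery. For the others it covers the six weeks after a completed cast period. These are different phases of recovery.

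At stake are precision and power. The protocol selects two factors as worth controlling at allocation and then gives up the precision this could bring. It names the test itself, so this is not merely a detail left to an analysis plan.

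**Working it through.** **Inputs from the Sample size calculation section.** Difference 11.5, SD 15.9, two-sided alpha 0.05, power 90%, 1:1 allocation, 42 per group, 92 in total with 10% dropout.

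**The plan's own figure.** The exact two-sample t-test needs 41.16 per arm, rounded up to 42, with power 90.6% at 42. So 42 per group is reproduced. For dropout, 84 × 1.1 = 92.4 and 84 / 0.9 = 93.3; the stated 92 is close to both.

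**Case A: 15.9 is the within-stratum SD.** Assumptions: 84 analysed patients, two equal strata, a gap g between strata in PRWE change. The gap is not given, so a range is used.

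- True SE of the difference under stratified allocation: 15.9 × √(2/42) = 3.47.
- Variance between strata: g²/4. The unadjusted test works with SD √(15.9² + g²/4).
- SE ratio: √(1 + (g²/4)/252.81), where 15.9² = 252.81.
- Approximate type I error: 2 × [1 − Φ(1.96 × ratio)].
- Approximate power: Φ(11.5/3.47 − 1.989 × ratio), with 11.5/3.47 = 3.314 and 1.989 the t quantile on 82 df.

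For g = 10, the ratio is √(1 + 25/252.81) = 1.048 and power is Φ(3.314 − 2.085) = 89.0%.

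| Gap in change | SE ratio | Type I error, formula | Type I error, simulated | Power, formula | Power, simulated |
|---|---|---|---|---|---|
| 5 | 1.012 | 4.7% | 4.8% | 90.3% | 90.4% |
| 10 | 1.048 | 4.0% | 4.0% | 89.0% | 88.9% |
| 15 | 1.106 | 3.0% | 3.0% | 86.8% | 86.7% |
| 20 | 1.181 | 2.1% | 2.1% | 83.3% | 82.7% |

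The simulation used 20,000 trials per gap. The model with strata held type I error near 5% and power at 90.6 to 90.9% throughout, including at a gap of zero.

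**Case B: 15.9 is the total SD.** Here the range is the share of outcome variance explained by the strata (R²), also an assumption. The adjusted SE is 15.9 × √((1 − R²) × 2/42). Power comes from 8,000 simulated trials per setting, with blocks of four within four age-by-treatment strata (shares 30/20/30/20%, equal additive effects of the two factors).

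| R² | Unadjusted SE | Adjusted SE | Unadjusted power | Adjusted power |
|---|---|---|---|---|
| 5% | 3.47 | 3.38 | 91% | 92% |
| 10% | 3.47 | 3.29 | 92% | 93% |
| 20% | 3.47 | 3.10 | 93% | 95% |
| 30% | 3.47 | 2.90 | 94% | 97% |

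Unadjusted type I error in Case B was 4.7, 4.1, 2.8 and 2.1%. The same four-stratum simulation with 15.9 as the within-stratum SD gave unadjusted power of 89, 88, 86 and 81%, against about 90% adjusted, in line with Case A.

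All figures are for the t-test. The Mann-Whitney branch was not simulated; it too has no stratum terms.

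**The case against.** The strongest reply is that the test is on change, so a PRWE gap between strata that is equal at T0 and T2 cancels and costs nothing. This stands. A reader might infer that any PRWE difference between operated and cast-treated, or younger and older, patients costs power. The protocol does not support that: the difference must be in change, and no figure for it is given.

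A reader might also infer that power necessarily falls below 90%. It does not. It stays at about 90.4% with a 5-point gap in Case A, and at 91 to 94% in Case B. The protocol also used the larger of two reported SDs (15.9 and 13.9). With their pooled value of 14.9 as the within-stratum SD, simulated unadjusted power is 93.5, 92.3, 89.6 and 86.5% at gaps of 5, 10, 15 and 20, so the target is essentially kept up to about 15 points. A loss against the adjusted test remains there: about 1.5 points of power at a gap of 10 and 4 at 15.

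Third, it is tempting to say that 15.9 contains no variance between strata at all. The Sample size calculation section supports this only for treatment type. It says nothing about ages in the source trial, so age variance may already be included.

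Finally, the upper end of the range is demanding. A 20-point gap means that strata explain 100/352.81 = 28% of the variance, and it exceeds the 17.6-point difference (36.1 − 18.5) between arms in the cited trial.

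None of this removes the core: where the strata do differ in change, the planned standard error is too large, and adjustment costs almost nothing where they do not.

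**Conclusion.** The point holds as a loss of efficiency of unknown size. The planned test does not reflect the stratified allocation. If strata differ in PRWE change, its standard error and confidence interval are too wide and its true type I error lies below 5%. The treatment estimate is not biased by this, and false positives are not increased.

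On the Case A assumptions, the power lost against the adjusted analysis is about 2 points at a 10-point gap (88.9 against 90.6%), 4 at 15 (86.7 against 90.7%) and 8 at 20 (82.7 against 90.6%), and negligible at 5 or less. Reading 15.9 as close to a within-treatment-type SD is reasonable, since it comes from operated patients only while this trial also enrols cast-treated ones, but the protocol does not settle it. On the Case B assumptions the stated 90% is met and the gain from adjustment is about 1 to 3 points. Both cases carry 15.9 over to the change score, as the plan does.

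The change should be made because it is nearly free, not because the trial is shown to be underpowered.

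**What to change.** In the Data analysis section, replace the two-sample test of PRWE change with a linear model containing treatment group, age group (18–64, 65 or above) and treatment type (conservative, operative). Report the adjusted mean difference with its 95% confidence interval. If a rank test is kept for non-normal data, make it a stratified one, such as the van Elteren test. Carry both factors into the repeated-measures and generalised estimating equations models for the secondary outcomes.

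Hospital need not be added on this argument. It is not a stratification factor, and the Introduction says only that guidelines may lead to regimens that differ between hospitals.

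The cost is a change of wording and two degrees of freedom in the primary model. Both variables are known at randomisation, and neither the sample size nor data collection changes.

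### The primary test is chosen by a normality check on the trial's own data, so the confirmatory hypothesis and effect measure are not fixed in advance

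*Protocol article*

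**What the plan says.** All references are to the protocol article.

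- **Data analysis, outcome.** "The primary outcome is the PRWE score at 6 weeks", followed by "This outcome is represented as the change in outcome scores from T0 to T2 (delta, T2–T0").
- **Data analysis, test.** "Data will be analysed using a two-sided t-test or the Mann-Whitney U test, depending on normality of the distribution". The article does not say how normality is judged, at what threshold, by arm or pooled, or before or after imputation. It names no effect estimate for either test.
- **Data analysis, missing data.** "An intention-to-treat analysis is performed, and any missing data are imputed". Multiple imputation is named only in the later paragraph on secondary outcomes.
- **Sample size calculation.** The trial is sized "for a two-sided t-test in two groups with an alpha of 0.05, a power of 90% (1–beta=0.9), an allocation ratio of 1:1", "using the SD of 15.9", giving "42 patients per group to detect a clinically relevant difference of 11.5 points at 6 weeks". No rank test enters the calculation.

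No other section fixes the primary test.

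**The concern.** A confirmatory trial should state beforehand which hypothesis it tests and which quantity it reports. Here both depend on the shape of the observed outcome data.

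If the t-test is used, the result is a mean difference in PRWE points. It can be set directly against the 11.5 points that the sample size section treats as clinically important. If the Mann-Whitney U test is used, the null hypothesis concerns the ordering of the two distributions. A significant result then says that one group tends to score lower than the other, and the plan names no PRWE-point estimate to show by how much.

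At stake is the meaning of the primary result. Two trials run to this plan could report different kinds of conclusion, and in some data sets the choice of test would decide whether the result counts as significant.

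**Working it through.** **1. The plan's own sample size.** Inputs from the sample size section: difference 11.5, SD 15.9, two-sided alpha 0.05, power 90%, 1:1 allocation.

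- Normal approximation: n = 2 × (1.960 + 1.282)² × (15.9/11.5)² = 2 × 10.51 × 1.912 = 40.2, so 41 per group.
- Noncentral t: 41.16, so 42 per group, with power 0.906 at 42.

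The stated 42 is reproduced, and it belongs to the t-test branch. If Mann-Whitney were the only test and the data were normal, its relative efficiency of 3/π would give 41.16 × π/3 = 43.1, so 44 per group. The difference is small.

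**2. Do the two branches test the same thing?** Simulation with 42 per arm and SD 15.9. The assumed rule is Shapiro-Wilk at 0.05 in each arm, moving to Mann-Whitney if either arm fails.

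| Assumed data | Rule picks Mann-Whitney | t-test rejects | Mann-Whitney rejects | Two-stage rule rejects |
|---|---|---|---|---|
| Normal, no difference | 10% | 0.049 | 0.048 | 0.049 |
| Normal, difference 11.5 | 10% | 0.902 | 0.886 | 0.900 |
| Gamma (mean 18.5) in both arms, no difference | >99% | 0.049 | 0.044 | 0.044 |
| Gamma, shifted by 11.5 | >99% | 0.89 | 0.98 | 0.98 |
| Gamma against normal, equal means and SDs | 98% | 0.051 | 0.085 | 0.085 |

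The last row is a constructed case. It shows that the rank test can respond to a difference in shape when the mean PRWE difference is zero, so the hypotheses differ. Where the two arms have the same distribution, type I error stays near 0.05. Row 3 also shows that the t-test keeps its level under marked skew at this sample size.

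**3. How often would the test switch on the change score?** Assumptions, none of them in the article: gamma-shaped 6-week scores with means 30 and 18.5 (difference 11.5) and SD 15.9; normal baseline with SD 15.9; Shapiro-Wilk in each arm on the change score; 42 per arm; 3,000 trials for each baseline-to-6-week correlation r.

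| | r = 0.2 | r = 0.3 | r = 0.5 |
|---|---|---|---|
| Two tests disagree on significance | 7% | 6% | 4% |
| Power, fixed t-test on change | 0.74 | 0.79 | 0.89 |
| Power, two-stage rule | 0.76 | 0.81 | 0.91 |
| Power, ANCOVA with HC3 standard errors | 0.90 | 0.90 | 0.95 |

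Over repeated runs the test switched in roughly 27–32% of trials. Under the null, the two-stage rule rejected in about 5%.

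**4. Where the power difference comes from.** The two-stage rule does no worse than the fixed t-test on change, so dropping the normality check recovers no power. The gap to ANCOVA comes from the baseline:

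- SD of a change score = 15.9 × √(2(1 − r)) = 20.1, 18.8, 15.9 for r = 0.2, 0.3, 0.5.
- Residual SD after baseline adjustment = 15.9 × √(1 − r²) = 15.6, 15.2, 13.8.

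**The case against.** The strongest defence is that discretion is limited. Both tests are named beforehand, both are two-sided, and the strengths and limitations list says that the analysing statistician is blinded to group. The choice follows distribution shape, not the more favourable p-value, and the detail of the normality check may sit in an analysis plan that is not shown. This stands as far as it goes: the rule does not invite selective reporting. It does not remove the defect, because the article itself states that the data pick the test, and blinding does not make a rank hypothesis and a mean hypothesis the same.

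A reader might infer several stronger points that the documents do not support:

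- **That the rule costs power or inflates type I error.** It does neither materially under the distributions tried, apart from the constructed unequal-shape case.
- **That the plan's figures show the tested variable to be skewed.** The source is "PRWE scores of 18.5 (SD 15.9) for the home-exercise group, compared with 36.1 (SD 13.9) in the physiotherapy group after 6 weeks". With mean 18.5 and SD 15.9, zero lies 18.5/15.9 = 1.16 SD below the mean. But these are raw 6-week scores from an earlier trial. The tested variable is the change, which has no floor at zero.
- **That a rank result could never be read against 11.5.** A Hodges-Lehmann shift with a confidence interval is in PRWE points and could be reported. The article simply names none.
- **That Mann-Whitney is inferior because it ignores baseline and strata.** The two-sample t-test ignores them equally.
- **That the test cannot be pooled over imputations.** This presumes multiple imputation for the primary outcome, where the article says only that missing data are imputed.

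**Conclusion.** The point holds as a defect of specification. The primary hypothesis and its effect measure are left to the observed data, while the trial was sized for one of the two branches only.

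Its practical size is moderate: a switch in roughly 27–32% of trials and opposite significance verdicts in about 4–7%. These figures rest on the assumed gamma scores, normal baseline and Shapiro-Wilk rule. Under normal data the switch rate falls to about 10%; under strong skew in the analysed variable it approaches 100%. The conclusion that the hypothesis is not fixed depends on none of these figures.

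The higher power of ANCOVA (about 0.90–0.95 against 0.74–0.89 for a t-test on change, under the same assumptions) is a benefit of baseline adjustment. It is not damage done by the normality check.

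**What to change.** Replace the sentence on the test with one prespecified primary analysis that estimates the mean PRWE difference between groups at 6 weeks, with a 95% confidence interval. The preferred form is a linear model (ANCOVA) of the 6-week score, adjusted for baseline PRWE, with heteroscedasticity-robust standard errors. A fixed two-sided t-test would also settle the hypothesis and match the sample size section, but would forgo the gain from baseline adjustment.

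Keep the Mann-Whitney U test as a sensitivity analysis that cannot replace the primary result. If it is reported, add a Hodges-Lehmann shift with its confidence interval so that it is expressed in PRWE points.

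The cost is one sentence. With about 42 per arm, inference on means does not need normal outcomes. The sample size stays as it is, and the model uses only baseline and 6-week scores that the primary analysis already requires.

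### Secondary repeated measures ANOVA makes pre-randomisation baseline a response level and ties no adjusted between-group contrast to PRWE at 2 and 12 weeks

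*Protocol article*

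**What the plan says.** The Data analysis section of the Protocol article gives one model for a group of outcomes: "For the secondary continuous outcomes (PRWE score at 2 and 12 weeks, ROM, grip strength, pain scores), a repeated measures analysis of variance" is to be performed. Treatment group is the only factor that varies between patients. The factor that varies within a patient has four levels: "time of visit (baseline, 2, 6 or 12 weeks follow-up) is the within-subjects factor". Baseline is therefore one of four values of the response and not a covariate. The Randomisation section fixes its timing: "After baseline measurements, the local researcher contacts the central research coordinator for randomisation to take place".

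The same paragraph offers an alternative: "In case of a non-normal distribution, generalised estimating equations will be used". It sets the threshold for secondary outcomes: "p values of <0.0045 will be considered statistically significant". It does not say which term of the ANOVA is judged against that threshold, and it does not mention the baseline value or the two stratification factors (age group and treatment type) as covariates.

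**The concern.** Two of the named secondary outcomes are visit-specific: PRWE at 2 weeks and PRWE at 12 weeks. The stated model has two standard tests that involve group, and neither is a test at one visit.

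- The **group main effect** averages the between-group difference over four visits, one of which precedes randomisation and has a true difference of zero.
- The **group-by-time interaction** asks whether the difference varies across the four visits. It does not say at which visit, and for PRWE it includes the 6-week visit, which is the primary endpoint.

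A p value below 0.0045 from either term could thus be reported under the label PRWE at 12 weeks without evidence specific to 12 weeks. Baseline is also placed where it cannot sharpen the follow-up comparison as a covariate would, and the threshold is already strict. The same model serves ROM, grip strength and pain. The switch to GEE after a look at the distribution adds a data-dependent choice of method and, as written, leaves the role of baseline unchanged.

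**Working it through.** **Inputs from the Protocol article.** Difference of 11.5 points, SD 15.9, 42 per group (Sample size calculation); threshold 0.0045 and four time levels (Data analysis).

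**Assumptions not in the document.** Same SD at every visit; compound symmetry with within-patient correlation ρ = 0.3, 0.5 or 0.7; true difference 0 at baseline and 11.5 at 2, 6 and 12 weeks.

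**The plan's own figures.** A two-sided t-test at 0.05 with 90% power for 11.5/15.9 needs 41.16, so 42 per group, as stated. The total of 92 agrees with 82/0.9 = 91.1 rounded up (84/0.9 would give 94). 0.05/11 = 0.00455 agrees with the threshold. None of these depends on the present point.

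**Size of the main effect.** (0 + 11.5 + 11.5 + 11.5)/4 = 8.625 points, which is 75% of 11.5. If the effect were 5.75 at 2 weeks and 11.5 afterwards, the four-visit mean would be 28.75/4 = 7.2, against a follow-up mean of 28.75/3 = 9.6.

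**What the interaction can and cannot distinguish.** Its noncentrality is (n/2)·Σ(e − ē)²/[SD²(1 − ρ)], where e is the difference at each visit.

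- Effect at all three follow-up visits: deviations −0.75, 0.25, 0.25, 0.25 (times 11.5). The sum of squares is 0.75 × 132.25 = 99.19.
- Effect at 6 weeks only: deviations −0.25, −0.25, 0.75, −0.25 (times 11.5). The sum of squares is again 99.19.

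At ρ = 0.5 both give 21 × 99.19/(252.81 × 0.5) = 16.5. The test has the same power whether the effect lasts through 12 weeks or exists at 6 weeks alone.

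**Power at alpha 0.0045** (noncentral F; 82 denominator df for the 1-df tests, 246 for the interaction). Variance of the between-group contrast is 2/42 times:

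- main effect: SD²(1 + 3ρ)/4, contrast 8.625
- single visit, unadjusted: SD², contrast 11.5
- single visit, change from baseline: 2·SD²(1 − ρ), contrast 11.5
- single visit, baseline-adjusted: SD²(1 − ρ²), contrast 11.5

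| Test | ρ = 0.3 | ρ = 0.5 | ρ = 0.7 |
|---|---|---|---|
| Group main effect, four visits | 75% | 59% | 47% |
| Group-by-time interaction, 3 df | 52% | 74% | 96% |
| Single visit, unadjusted | 65% | 65% | 65% |
| Single visit, change from baseline | 46% | 65% | 91% |
| Single visit, baseline-adjusted | 71% | 81% | 95% |

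Example at ρ = 0.5: the adjusted contrast has standard error 15.9 × √(2/42 × 0.75) = 3.00, against 15.9 × √(2/42) = 3.47 unadjusted. Among the three visit-specific contrasts, the adjusted one is the most powerful at every correlation tried.

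**Can the planned model give visit differences?** Yes. In a simulated data set, a group-by-visit model on all four visits returned exactly the observed between-group difference at each visit (for example −4.1 at 2 weeks and −10.2 at 12 weeks). These are the unadjusted differences.

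**The case against.** The strongest reply is that the model is sound and only its reporting is left open. Four points of it stand.

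- A reader might infer that the ANOVA cannot estimate the 2- and 12-week differences. That is not so: they are ordinary contrasts of a group-by-visit model, and a full analysis plan could name them. An article's silence about contrasts would not by itself be a fault.
- A reader might infer that the treatment effect is diluted outright. The text never says that the group main effect is the test. With baseline as a time level, the interaction is the usual treatment test, and a zero effect at baseline does not dilute it.
- The power comparison depends on the correlation. Against the interaction, the adjusted visit contrast gains at 0.3 and 0.5 and has no advantage at 0.7 (95% against 96%). At 0.3 the main effect has slightly more power than the adjusted visit contrast (75% against 71%), though for a different quantity. The baseline-adjusted mean of the three follow-up visits reaches 98/99/99.8%, but it is not a visit-specific difference and is no fair yardstick here.
- The visit-specific argument applies to PRWE. ROM, grip strength and pain are listed in that section without a visit, and a longitudinal test suits them reasonably well. Use of the 6-week data in the model is no fault in itself, since the model proposed below also uses them.

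The reply does not remove the model that the text does fix: a four-level time factor with pre-randomisation baseline as a response, and neither baseline nor the strata as covariates. Contrasts added later to that model would answer the right question with less precision than the same data allow.

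**Conclusion.** The point holds as a free improvement to the secondary analyses. The plan treats pre-randomisation baseline as one of four outcome levels and links no between-group contrast to PRWE at 2 and 12 weeks. The consequence depends on the term used: a constant effect reduced to 75% (11.5 to 8.6 points) under the main effect, or a 3-df answer with no visit attached under the interaction. With visit contrasts the question is answered, but baseline adjustment would raise power from 65% to 71%, 81% or 95% at correlations of 0.3, 0.5 and 0.7.

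These figures assume 11.5 points at every follow-up visit, SD 15.9 throughout, 42 per group, alpha 0.0045 and compound symmetry; the correlation is not in the document. The documents do not support a claim that the visit differences are inestimable or that dilution is certain. The primary 6-week PRWE comparison is a separate two-group test on change and is not affected.

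**What to change.** Replace the repeated measures ANOVA for the secondary continuous outcomes with a linear mixed model of the 2-, 6- and 12-week values. Include treatment, visit, treatment-by-visit, the baseline value of the outcome, and the stratification factors age group and treatment type. Report the adjusted between-group difference with 95% CI at each named visit, which for PRWE means 2 and 12 weeks, and judge those contrasts against the secondary threshold. Use this model whatever a normality check shows, with robust standard errors if needed, so that the method does not depend on the data.

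The cost is a change of analysis wording. No extra visits, measurements or patients are needed, and the primary analysis and sample size stay as they are.
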